## Statistical methods

In the final analysis of the results a so-called “evaluation of increment” will take place. Change in ADAS-cog score (primary outcome measure) of every patient will be compared between two groups by means of a 2 x 2 ANOVA (categories: group, time;  = 0.05).

Secondary outcome measures will be analyzed following the same procedure, with correction for multiple equations.

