# Study design

A randomized double blind, placebo-controlled, multicenter clinical trial to evaluate the effect of indomethacin over a one year period on the progression of mild to moderate Alzheimer’s disease. Following screening and baseline assessments, 160 patients will either receive indomethacin or placebo.

Evaluation of the ability of indomethacin to retard disease progression will be performed in weeks 26 and 52 (ADAS-cog/non-cog, MMSE, CIBIC+, NPI and IDDD). Safety en tolerability evaluations will be performed in weeks 4, 8, 26 and 52 (adverse events, physical examination, vital signs and laboratory evaluations). The evaluation schedule is specified in Appendix III.

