# Statistical considerations

## Sample size

For estimation of the required sample size, the following assumptions were made:

- patients deteriorate 5.0 points (SD 7.0) on the ADAS-cog in one year.
- a difference of 3.0 points or more regarding the changes from baseline is considered to be clinically relevant in case indomethacin is tested against placebo.
- power of 80 percent.
- statistical testing will be done one-sided, at a significance level of 0.05.

Based on the above statistical considerations, a total of 67 patients per group will be necessary. Assuming a dropout rate of 20 percent, the total sample size will be 160 patients (80 patients per group).

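### Section 12.3 does not tie the primary 2 x 2 group-by-time ANOVA to the one-year ADAS-cog difference for which the trial is sized: the time levels, the deciding term and the error unit are left open.

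*Protocol*

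**What the plan says.** Section 12.3 makes change in ADAS-cog the response and says it will be "compared between two groups by means of a 2 x 2 ANOVA (categories: group, time"), at a level of 0.05. It stops there.

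Section 4 sets the efficacy visits: "Evaluation of the ability of indomethacin to retard disease progression will be performed in weeks 26 and 52". The evaluation schedule in Appendix II agrees, with ADAS-cog at baseline, week 26 and week 52 only.

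Section 12.1 sizes the trial on one year. It assumes that "patients deteriorate 5.0 points (SD 7.0) on the ADAS-cog in one year", that "a difference of 3.0 points or more regarding the changes from baseline is considered to be clinically relevant", a "power of 80 percent", and that "statistical testing will be done one-sided, at a significance level of 0.05". From these it concludes that "a total of 67 patients per group will be necessary".

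**The concern.** The response is already a change from baseline, and such changes exist at exactly two times. The natural reading of a two-level time factor is therefore week 26 and week 52. Neither of the terms that involve treatment in that ANOVA is the contrast used for the sample size.

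Two things are at stake. The trial could be decided by a term with a different target and, under plausible assumptions, less power than planned. And because the deciding term is not named, the choice between group and interaction could be made after the data are seen. The error unit is also unstated, and the type I error depends on it, because each patient contributes two correlated values.

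**Working it through.** **Inputs from the protocol.** Difference 3.0 points, SD 7.0 for one-year change, one-sided 0.05, power 80%, 80 randomised per group, 20% dropout (section 12.1). ADAS-cog at weeks 0, 26 and 52 (Appendix II).

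**Assumptions, because the protocol gives no figure.** Linear divergence, so 3.0 x 26/52 = 1.5 points at week 26. Week-26 SD s of 5 to 7. Correlation r between a patient's two changes of 0.5 to 0.8 for power and 0.3 to 0.9 for type I error. Evaluable patients 80 x 0.8 = 64 per arm.

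**1. The plan's own figure.** n = 2 x 7² x (1.645 + 0.842)² / 3² = 67.3 per group, which agrees with the stated 67 to within rounding. The sample size is thus that of a direct one-sided two-group comparison of one-year change. The two-sided version needs 86 per group.

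**2. Literal reading: changes at weeks 26 and 52, patient as error unit.**

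- Group term: target (1.5 + 3.0)/2 = 2.25 points; SD = √(49 + s² + 14rs)/2.
- Interaction: target 3.0 − 1.5 = 1.5 points; SD = √(49 + s² − 14rs).
- Week-52 contrast: target 3.0 points; SD 7.

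The standard error is SD x √(2/64) = SD x 0.177. Power is from the noncentral t, one-sided 0.05.

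| Term | s, r | SD | Target/SE | Power |
|---|---|---|---|---|
| Group | 5, 0.5 | √109/2 = 5.22 | 2.44 | 78% |
| Group | 7, 0.8 | √176.4/2 = 6.64 | 1.92 | 60% |
| Interaction | 7, 0.5 | √49 = 7.00 | 1.21 | 33% |
| Interaction | 5.25, 0.8 | √17.76 = 4.21 | 2.01 | 64% |
| Week 52 alone | – | 7.00 | 2.42 | 78% |

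**3. Other reading: raw scores at baseline and week 52.** In a repeated-measures ANOVA the group x time F equals the square of the t statistic for one-year change (0.4589 for both on test data). This term does test the one-year difference. It makes no use of week 26 and loses every patient without a week-52 score.

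**4. Type I error if a patient's two changes were treated as independent.** The true variance of the group contrast is f = 1 + 2rq/(1 + q²) times the assumed one, with q = s/7. The error rate is P(|Z| > 1.960/√f) two-sided, or P(Z > 1.645/√f) one-sided.

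| s | r | f | Two-sided | One-sided |
|---|---|---|---|---|
| 5 | 0.3 | 1.28 | 0.084 | 0.073 |
| 7 | 0.3 | 1.30 | 0.086 | 0.075 |
| 7 | 0.5 | 1.50 | 0.110 | 0.090 |
| 7 | 0.9 | 1.90 | 0.155 | 0.116 |

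Simulation with 67 per arm and s = 7 gave two-sided rates of 0.082, 0.110 and 0.158 at r = 0.3, 0.5 and 0.9. The interaction term moves the other way: 0.019 at r = 0.3 and 0.006 at r = 0.5. With the patient as error unit, the simulated rate was 0.047 to 0.053.

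**The case against.** The best defence is that section 12.3 can be read as a pre/post layout. It introduces the analysis as an evaluation of increment, section 12.1 is framed on one year, and a repeated-measures interaction on baseline and week 52 is exactly the comparison that was sized. This stands, so a reader should not infer that the planned analysis cannot test the one-year difference. But the stated response is change, which fits weeks 26 and 52 better, and nothing in the section settles the matter.

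A reader might also infer that the plan more than doubles the false-positive rate. The protocol does not support that. It never says that a patient's values are treated as independent, though it does not exclude it. Even then, with equal SDs, the two-sided rate passes 0.10 only when r exceeds (1.960/1.645)² − 1 = 0.42. At the one-sided level that section 12.1 states, the threshold is (1.645/1.282)² − 1 = 0.65. No correlation is given.

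Nor does every reading drop a patient who misses one visit. A complete-case repeated-measures ANOVA on weeks 26 and 52 does. A plain two-way ANOVA keeps the available row, and the baseline/week-52 reading loses only those without week 52.

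Finally, averaging two visits need not cost power. At s = 5.25 and r = 0.3 the group term reaches about 82% with 64 per arm, above the week-52 contrast. That is fair, but the term would still estimate a different quantity. Model detail such as a covariance structure may properly sit in a statistical analysis plan. The primary contrast is different, because the protocol has already fixed a test and left its meaning open.

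**Conclusion.** The concern holds as a mismatch on the literal reading and as an ambiguity overall. With changes at weeks 26 and 52, neither treatment term is the contrast behind the sample size. That conclusion rests on the protocol alone. The size of the power loss rests on the assumed linear divergence, week-26 SD and correlation: at worst the interaction has about one-third power, while the group term ranges from 60% to no loss.

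The type I error is a conditional risk. It is about 0.08 to 0.16 two-sided, or 0.07 to 0.12 one-sided, and arises only if the group term decides and the two changes are analysed as independent. Since this is the primary test, the wording should be settled before any unblinded analysis.

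**What to change.** Replace the sentence in section 12.3 so that the primary test is the treatment difference in ADAS-cog change at week 52, with the patient as error unit and the sidedness of section 12.1 stated. Sidedness matters because an ANOVA F-test is two-sided by construction: at 67 per group, two-sided 0.05 gives about 70% power for the week-52 contrast, against about 80% one-sided.

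A suitable model is a mixed model for repeated measures on the changes at weeks 26 and 52, with treatment, visit, treatment x visit and baseline ADAS-cog, and an unstructured within-patient covariance. Include all randomised patients with any post-baseline ADAS-cog. Other models with the same contrast and error unit would also serve.

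The cost is one paragraph of protocol text and slightly more analysis work. No new data are needed.

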## Interim analysis

An interim analysis of the intended effect of indomethacin will not be conducted, considering the size of the studied population and the size of the expected effect.

# Study records

## Confidentiality

Study records will be considered medical information and thus confidentiality should be maintained. Should knowledge of patient identity become necessary for safety or regulatory reasons, confidentiality by the Investigator will be maintained.

## Storing of study records

During the study term the study records will be stored appropriately to ensure their confidentiality. They will remain in the possession of the investigator and must be kept for period of ten years.

# Publication of results

The study results will be presented to peer-reviewed journals for publication. All of the contributors named in the study proposal will be listed as co-authors. Anonymity and privacy of the patients will be guaranteed. If results are relevant to the society, the department “PR en Voorlichting” will be contacted for publication in the public media.

## Study location

Primary assessment of patients will take place at the outpatient clinic for memory disorders at the Department of Geriatric Medicine, University Hospital Nijmegen. Following assessments will take place either at the outpatient clinic or at the patient’s home, depending on his/her condition.

**APPENDIX II**

**Evaluation Schedule**

| **Evaluations** | **Screening** | **Baseline** | **Week 4** | **Week 8** | **Week 26** | **Week 38** | **Week 52** |
| --- | --- | --- | --- | --- | --- | --- | --- |
|  | **Week -2** | **Week 0** |  |  |  |  |  |
| NINDS/ADRDA criteria | X |  |  |  |  |  |  |
| DSM-IV criteria | X |  |  |  |  |  |  |
| MMSE | X | X |  |  | X |  | X |
| CT/MRI-brain | (X) |  |  |  |  |  |  |
| NINDS/AIREN criteria | X | (X) |  |  |  |  |  |
| Medical History | X |  |  |  |  |  |  |
| Medication | X |  |  |  |  |  |  |
| Physical Examination | X |  | X |  | X |  | X |
| Blood pressure/weight | X | X | X |  | X |  | X |
| Blood test | X |  | X | X | X |  | X |
| APO-E phenotyping | (X) |  |  |  |  |  |  |
| EKG | (X) |  |  |  |  |  |  |
| In/exclusion criteria | X | (X) |  |  |  |  |  |
| Informed consent |  | X |  |  |  |  |  |
| Randomisation number |  | X |  |  |  |  |  |
| ADAS-cog |  | X |  |  | X |  | X |
| ADAS-non cog |  | X |  |  | X |  | X |
| CIBIC+ |  | X |  |  | X |  | X |
| NPI |  | X |  |  | X |  | X |
| IDDD |  |  |  |  |  |  |  |
| Adverse events checklist |  |  | X | T | X | T | X |
| Distribution of indomethacin |  | X | X |  | X |  |  |
| Distribution of omeprazole |  | X | X |  | X |  |  |
| Indomethacin diary |  | X | X |  | X |  | X |
| Change in concomitant medication? |  | X | X | T | X | T | X |
| Change in medical condition? |  | X | X | T | X | T | X |

T = assessment by telephone

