## Inclusion criteria

- The patient will satisfy the DSM-IV criteria for dementia of the Alzheimer’s type.
- The patient will satisfy the NINCDS/ADRDA criteria for the clinical diagnosis of probable Alzheimer’s disease (Appendix I)20.
- The severity of dementia for each patient will be quantified by a Mini-Mental State Examination (MMSE) score between 10 and 26 (both inclusive).
- The patient is living at home or in a home for the elderly.
- The patient has a responsible caregiver who is able to provide information about the patient’s functional status.
- Written informed consent is obtained from the patient or the legally accepted representative.

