## Eligibility screening

Screening will be conducted at least 14 days before the patient begins taking study medication. Patients must satisfy the DSM-IV criteria for dementia of the Alzheimer type. Patients must also satisfy the NINCDS-ADRDA criteria for probable Alzheimer’s disease, have a MMSE score between 10 and 26 (both inclusive) and have a responsible caregiver to ensure compliance with the protocol.

To be eligible for the study, patients must satisfy selection criteria. Potentially eligible patients whose screening examinations show any disqualifying abnormality may have their examination to be repeated. Results must be within normal limits or judged not clinically significant before the patient starts treatment with the study medication.

Patients will undergo the following screening assessments (Appendix II): medical history, prior and concomitant medications or therapies, physical examination, vital signs, laboratory evaluations (including Apo E genotyping) and MMSE. Evaluation of the urine, electrocardiogram and CT scan of the brain will be conducted when not performed recently (CT scan > 2 years).

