## Informed consent

All patients (if possible) and (if appropriate) a legally acceptable representative on the patient’s behalf and the patients caregiver will be fully informed about the study, orally and in writing. Each patient, if mentally competent, or a legally acceptable representative on the patient’s behalf, if appropriate, shall provide written consent before the patient may participate. Should the patient not be capable of providing written informed consent, written consent must be obtained from the legally acceptable representative on the patient’s behalf and verbal assent must be provided by the patient (Appendix III, IVa and IVb).

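### Appendix II schedules informed consent only at Baseline, after the screening procedures, although consent is an inclusion criterion that the same table checks at Screening

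*Protocol*

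**What the plan says.** **Appendix II (Evaluation Schedule).** The first two columns are Screening, Week -2, and Baseline, Week 0. The consent row reads "Informed consent | | X": the Screening cell is empty and the only mark is under Baseline. The blood test row reads "Blood test | X | | X | X | X | | X", with a plain mark at Screening and none at Baseline. Physical examination and MMSE also have plain marks at Screening. Apo E is bracketed there ("APO-E phenotyping | (X"), as are EKG and CT/MRI. The inclusion and exclusion criteria have a plain mark at Screening and a bracketed one at Baseline.

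**Section 5.2.** One inclusion criterion is: "Written informed consent is obtained from the patient or the legally accepted representative".

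**Section 5.6.** "Screening will be conducted at least 14 days before the patient begins taking study medication". The assessments that patients undergo at screening include "laboratory evaluations (including Apo E genotyping) and MMSE". Some other items are conditional: "Evaluation of the urine, electrocardiogram and CT scan of the brain will be conducted when not performed recently".

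**Section 7.4.** The patient, if mentally competent, or a representative "shall provide written consent before the patient may participate". Where the patient cannot consent in writing, the representative's written consent and the patient's verbal assent are both required.

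**The concern.** Site staff commonly work from the schedule table. A site that follows this one would examine patients with dementia, take blood and possibly test Apo E about two weeks before the only consent that the table provides for. It would also tick off the inclusion criteria at a visit where one of them cannot yet be met.

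What is at stake is patient protection. The safeguard in 7.4 for patients who cannot consent themselves would come after the screening procedures. A patient who fails screening, or who declines at Baseline, could have been tested for the trial without having agreed to it.

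**Working it through.** No power or sample-size figure is involved. The check is a reading of the table followed by a comparison of sections.

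**1. Is the consent mark really under Baseline?** The consent row has seven cells after its label, like the other rows, and the mark is in the second. The blood test row is a control. Read in the same way, it gives Screening and weeks 4, 8, 26 and 52, and the four post-baseline weeks are those that section 4 names for safety evaluations, including laboratory tests. The columns have therefore not shifted.

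**2. How far apart are the two visits?** Week 0 − (Week -2) = 2 weeks = 14 days. The 14 days in 5.6 run from screening to first study medication, not to consent. Medication is first distributed at Baseline, the column that also holds consent, so the nominal gap from screening to consent is also two weeks.

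**3. Appendix II against 5.2.**

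| Item | Screening (Week -2) | Baseline (Week 0) |
| --- | --- | --- |
| Inclusion/exclusion check | X | (X) |
| Written consent (a criterion under 5.2) | – | X |

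At the unconditional check, the consent criterion cannot be satisfied by a patient who follows the schedule. This holds however the word participate in 7.4 is read.

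**4. Appendix II against 7.4.** The outcome depends on when participation starts, and 7.4 does not say. If it starts with screening, the schedule contradicts 7.4. If it starts at Baseline, the two agree.

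**5. Which screening items are done for the trial?**
- Apo E status appears in neither the inclusion nor the exclusion criteria (5.2, 5.3). Its only stated use is the comparison of the groups in 12.2, so it serves research and not eligibility. Section 5.6 lists it without a condition, while Appendix II puts it in brackets that the table does not explain.
- Blood test and physical examination are unconditional in Appendix II. They may coincide with diagnostic work-up, but the protocol does not say so.
- EKG, urine and CT are needed only when there is no recent result (5.6).
- Section 5.6 allows a screening examination with a disqualifying abnormality to be repeated. Such a repeat is driven by eligibility.
- Section 5.5 allows recruitment through public media. Those patients need not be in work-up at the centres at all.

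**6. Is an earlier consent provided for elsewhere?** The text available has no separate screening consent and no exemption of screening tests from consent.

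**The case against.** **Participation may begin at Baseline.** Section 6.1 measures the patient's study duration from baseline. Section 8 gives participating patients a trial number, and Appendix II issues the randomisation number in the same column as consent. On that reading 7.4 is respected. This stands: a reader might infer an outright breach of 7.4, and the documents do not establish one. The six visits in 6.1 do not settle it. Appendix II has seven columns. Leaving out Screening gives 7 − 1 = 6, but leaving out Week 38, where every marked assessment is by telephone, also gives 7 − 1 = 6. Nor does this reading remove the conflict with 5.2.

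**The criteria are looked at again at Baseline.** True, but that mark is bracketed and the legend explains only the telephone code. The plain mark is at Screening.

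**Much of screening may be routine care.** Section 5.5 recruits mainly from memory and outpatient clinics, and most screening items could be part of an ordinary dementia work-up. This stands in part: not every screening item can be called trial-specific. It does not cover Apo E, for which no clinical or eligibility use is given.

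**The consent documents are not at hand.** Section 7.4 refers to appendices that are not in the text reviewed, and they may address screening. For that reason the point is limited to what the schedule and sections say, and it does not claim that anyone was in fact tested without consent.

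**A reader might infer a loss of Apo E data.** The documents do not support this. The comparison in 12.2 concerns the randomised groups, and under the schedule those patients have consented by the time they receive a randomisation number.

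**Conclusion.** The point holds as an internal conflict that bears on patient protection. Appendix II puts the only consent mark two weeks after the screening procedures. This conflicts with 5.2 as Appendix II applies it, and it fits poorly with 7.4. Followed literally, the schedule lets procedures done for the trial, notably Apo E testing, come before consent, and patients who fail screening may be tested without it.

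The unconditional items are scheduled for every patient, including all of the approximately 160 to be randomised. The bracketed items apply to an unknown share. The number of people screened but not randomised cannot be derived, because the protocol gives no screen-failure rate, so no total is offered here.

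The conclusion rests on two assumptions: that sites follow the table as printed, and that the consent documents not at hand do not provide for an earlier consent. The Apo E test is called genotyping in 5.6 and phenotyping in Appendix II (12.2 also speaks of phenotype). The point is the same under either name.

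There is no effect on the endpoint, the sample size or the analysis. It is still more than a clerical matter, because it determines what is done to patients before they or a representative agree.

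**What to change.** - In Appendix II, move the consent mark to the Screening column. A further mark at Baseline can be kept as reconfirmation.
- In 5.6, add a sentence that no procedure done only for the trial takes place before the consent described in 7.4, and that results already available from routine care may be used.

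This brings Appendix II, 5.2, 5.6 and 7.4 into line without having to define participation. It costs one table cell, one sentence and slightly earlier consent work, including for some patients who then fail screening. Design, randomisation and analysis stay as they are.

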## Side effects

The risk for gastrointestinal side effects related to the use of NSAIDs in elderly people is 20 percent. In patients of 50 years and older, using a high dosage of the NSAID indomethacin and using corticosteroids at the same time, the risk of serious gastrointestinal complications can be 10 times higher, especially during the first three months. To prevent possible gastrointestinal side effects, omeprazol (20 mg once a day) will be prescribed21.

The patient’s discomfort will be small when no inconvenient side effects occur. A (small) discomfort for the patient will be the puncture in order to get blood samples.

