## Measures taken in case of adverse events

An adverse event is any undesirable sign, symptom or medical condition occurring after starting the intake of the trial medication, whether considered drug-related or not. Medical conditions/diseases present before starting the trial medication are only considered adverse events if they worsened after starting the medication.

In case of an adverse event with a possible causal relationship to the use of indomethacin, the medical attendant (e.g. family physician, physician) will discontinue the trial medication. The trial ends, however the trial code will not be broken and the patient’s data will be analyzed. The medical attendant will be asked to report this decision to the investigators as soon as possible.

The medical attendant is allowed to lower the dose of the study medication, in case of a dubious causal relationship between the adverse event and the study medication. The trial code will not be broken and the patient will be considered a normal participator of the trial.

In case of a serious adverse event, the patient’s medical attendant will ask the pharmacist to announce the nature of trial medication. The code will then be broken, the medication will be discontinued and the patient’s data will not be included in the analysis of the final outcome measures. However, the data of patients discontinuing the trial will analyzed according to the “intention to treat” principle.

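### The adverse-events checklist has no pre-dose administration, so new or worsened minor symptoms are judged without a like-for-like baseline (minor, cheap to improve)

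*Protocol*

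**What the plan says.** **Definition.** Protocol section 10.3 (Measures taken in case of adverse events) ties an adverse event to onset after the first intake of trial medication. For conditions already there it adds: "Medical conditions/diseases present before starting the trial medication are only considered adverse events if they worsened after starting the medication".

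**Schedule.** In Appendix II (Evaluation Schedule) the columns run screening, baseline, then weeks 4, 8, 26, 38 and 52. The checklist row is "Adverse events checklist | | | X | T | X | T | X", where T means a telephone assessment.

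**Other pre-dose information in the same table.**
- History, at screening only: "Medical History | X".
- A question on change, first asked at baseline: "Change in medical condition? | | X | X | T | X | T | X".
- Examination: "Physical Examination | X | | X | | X | | X".
- Laboratory: "Blood test | X | | X | X | X | | X".
- Blood pressure and weight, at both screening and baseline.

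**Sources and use.** Section 11.1 (Monitoring of adverse events) also takes events from spontaneous reports, the investigator's questioning, examination and laboratory results. Safety and tolerability is a secondary objective (section 3.2). Section 9.4 gives one rate: "The risk for gastrointestinal side effects related to the use of NSAIDs in elderly people is 20 percent".

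**The concern.** To decide whether a symptom is new or worse, one needs its state before the first capsule. Section 4 (Study design) names four kinds of safety evaluation: adverse events, physical examination, vital signs and laboratory tests. The last three have a pre-dose entry in Appendix II. The adverse-events checklist does not.

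A checklist prompts, and an open history may not. A patient with long-standing mild headache or dyspepsia may not mention it at week -2. At week 0 the question is about change, and a stable complaint is not a change. The complaint may then be recorded for the first time at week 4. Its onset would have to be reconstructed by a patient whose MMSE at entry was between 10 and 26, or by the caregiver.

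At stake is the sharpness of the tolerability comparison. Old complaints counted as events add the same background to both arms and shrink the apparent excess on indomethacin. No later analysis can recover a pre-dose answer that was never collected.

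**Working it through.** **1. What the schedule supplies.** For each safety item, the pre-dose entries in Appendix II are:

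| Item | Screening | Baseline | First on treatment |
|---|---|---|---|
| Physical examination | yes | no | week 4 |
| Blood pressure/weight | yes | yes | week 4 |
| Blood test | yes | no | week 4 |
| Medical history | yes | no | not repeated |
| Change in medical condition | no | yes | week 4 |
| Adverse-events checklist | no | no | week 4 |

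The pre-dose record is therefore partial. It covers signs, laboratory values, reported history and reported change. It does not cover the checklist items as such.

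**2. Is there a figure to reproduce?** No. The protocol gives no power, hypothesis test or placebo rate for adverse events. The calculation below is only an illustration of dilution.

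**3. Inputs.**
- Indomethacin event rate 20%, borrowed from section 9.4. That is a general NSAID figure for elderly people, not a forecast for this trial with omeprazole.
- Placebo event rate 5% or 10%: assumed.
- 80 per arm (section 5.1).
- Two-sided 0.05: assumed for this comparison.
- q, the share of patients in each arm whose existing complaint is missed before dosing and then counted as an event: assumed, equal in both arms.

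**4. Formulas.** Observed rate p' = 1 − (1 − p)(1 − q). The observed difference is therefore the true difference times (1 − q).

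Power = Φ[(d − 1.96·SE0)/SE1], where d is the observed difference. SE0 uses the pooled rate, √[p̄(1 − p̄)(2/80)]. SE1 uses the separate rates, √[(p1(1 − p1) + p2(1 − p2))/80].

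**5. One line worked, 20% v 5% at q = 10%.**
- Indomethacin: 1 − 0.80 × 0.90 = 0.28. Placebo: 1 − 0.95 × 0.90 = 0.145. So d = 0.135.
- p̄ = 0.2125, SE0 = √(0.2125 × 0.7875 × 0.025) = 0.0647.
- SE1 = √[(0.2016 + 0.1240)/80] = 0.0638.
- Power = Φ[(0.135 − 0.1268)/0.0638] = Φ(0.13) = 0.55.

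**6. Results.**

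| q | Observed, true 20% v 5% | Risk ratio | Power | Observed, true 20% v 10% | Power |
|---|---|---|---|---|---|
| 0 | 20% v 5% | 4.0 | 82% | 20% v 10% | 42% |
| 2% | 21.6% v 6.9% | 3.1 | 76% | 21.6% v 11.8% | 38% |
| 4% | 23.2% v 8.8% | 2.6 | 70% | 23.2% v 13.6% | 35% |
| 10% | 28% v 14.5% | 1.9 | 55% | 28% v 19% | 27% |
| 20% | 36% v 24% | 1.5 | 38% | 36% v 28% | 19% |

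**7. Direction.** If the true rates are equal, the observed rates are equal at every q. Equal miscounting in both arms lowers the contrast and cannot produce a difference where none exists.

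**The case against.** The case for leaving the schedule alone has weight.

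- **A pre-dose record exists.** History, examination and blood tests precede dosing, change is asked at baseline, and section 10.3 says how existing conditions are handled. Gastrointestinal history also has to be explored, because past ulcer, gastric surgery or bleeding excludes the patient. This stands. A reader might infer from the blank cells that old complaints cannot be told from new ones; the protocol does not support that. What remains is the minor symptom that these steps miss.
- **The forms are not shown.** The checklist or the adverse-event form may carry onset date, prior presence or severity. If so, much of the problem shrinks, although the answers would still be retrospective.
- **Nothing is contradictory.** A post-dose adverse-event row fits a definition based on onset after dosing. That is correct. The point concerns an instrument that could be better used, not a wrong statement.
- **The numbers are assumed.** Neither the placebo rate nor q appears in the protocol, and q requires both a missed complaint and a later miscount. At small q the loss is modest.

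A reader might also infer that misdated complaints would lead to unjustified stopping, since section 10.3 says "In case of an adverse event with a possible causal relationship to the use of indomethacin, the medical attendant" will discontinue the medication. The documents do not support that step. Stopping follows the attendant's judgement of causality, not a tick on the checklist, and a dubious relationship is handled separately. Multiplying an assumed share by 80 would count patients with an old complaint, not mistaken stops.

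**Conclusion.** The point holds as a minor weakness in data collection for a secondary objective. The checklist is the one prompted adverse-event instrument and has no like-for-like pre-dose record, while section 10.3 requires a judgement of new or worsened. For minor symptoms not picked up by the history or the baseline change question, that judgement rests on a less structured record.

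The effect is dilution, expected to be similar in both blinded arms. Its size is unknown. Under the assumed 20% v 5%, power goes from 82% to about 76% if 2% of patients are miscounted, and to 55% or 38% only if 10% or 20% are. Under 20% v 10% it starts at 42% and falls to 27% or 19% at those shares. These figures show sensitivity and are not a forecast. The sample size and the primary ADAS-cog comparison are not touched.

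**What to change.** In Appendix II, mark the adverse-events checklist (X) at Baseline, to be completed before the first capsule with severity recorded per item. In sections 10.3 and 11.1, state that new or worsened is judged against that record together with the screening history.

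This uses an existing form at an existing visit and changes no clinical rule. The cost is a few minutes per patient and a slightly longer baseline visit.
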